## **1 Introduction**

---

### **1.1 Background**

Cataract and dry eye are two conditions occurring frequently in the elderly. Several reports suggested a deterioration of dry eye after cataract surgery, causing a significant impact on patients' postoperative satisfaction as well as quality of life.

Recently, a novel index, assessing the risk of developing dry eye after cataract surgery in a non-dry eye population, was published; the so called – Ocular Surface Frailty Index (OSFI).[1] This score utilizes 10 items including clinical ocular findings, medical history as well as environmental factors and grade the respective subject in low-risk- or high-risk group. Using the cutoff of 0.3, the rate of postoperative dry eye was 9,6% in the low-risk group and 50% in the high-risk group ( $p < 0.001$ ).

Systane Hydration MDPF eye drops (Alcon Research, Ltd., Fort, Worth, Texas, USA, a division of Novartis) is an artificial tear substitute based on the dual-polymer formula containing HP-Guar and hyaluronic acid. Previous studies found an increase in tear film stability and reduction of subjective complaints.[2]. In an animal model corneas treated with Systane Hydration showed the fastest re-epithelialization compared to other HA products supporting the beneficial role of HA-containing artificial tears in corneal wound healing.[3]

The current study seeks to investigate if intensive lubrication, using Systane Hydration MDPF, in the postoperative phase of cataract surgery can reduce the rate of dry eye in the high-risk group. The findings will have a great impact how to identify these patients, to administer the adequate therapy, which might hinder development of dry eye related to cataract surgery.

### **1.2 Risk/benefit assessment**

Lubricating eye drops have an excellent safety profile especially when preservative-free formulations are used. By adding lubrication to the treatment regime, the patients are not put to an additional risk. All study relevant procedures are used routinely in our department.

The risk/benefit ratio is acceptable.

Postoperativ verabreichte Lubrication-Augentropfen reduzieren die Rate an Symptomen des trockenen Auges nach Kataraktextraktion bei Patienten mit hohem Risiko (Ocular Surface

Frailty Index  $\geq 0,3$ ), Symptome des trockenen Auges zu entwickeln, im Vergleich zur Standardversorgung.

## 2 Study objective

---

### Hypothesis

Postoperatively administered lubrication eye drops reduce the rate of dry eye symptoms after cataract extraction in patients with high-risk (Ocular Surface Frailty Index  $\geq 0,3$ ) to develop dry eye symptoms compared to standard of care.

### **OBJECTIVES:**

The aim of this study is to compare the signs and symptoms of dry eye after cataract surgery between groups, patients with preoperatively high risk and low risk, and evaluate if adequate and frequently administered lubrication eye drops reduce the signs and symptoms of dry eye in patients with high risk compared to standard of care. The following 3 groups will be compared:

- **Group 1, high risk: Standard of care** OSFI  $\geq 0,3$ , NSAID (2x day for 4 weeks)
- **Group 2, high risk: Treatment** OSFI  $\geq 0,3$ , Systane Hydration MDPF eye drops (4 x day for 3 months) NSAID (2x day for 4 weeks)
- **Group 3, low risk: Reference** OSFI  $< 0,3$ , NSAID (2x day for 4 weeks)
  - **Primary objective:** To compare the rate of dry eye symptoms between Group 1 and Group 2 at 3 months (after cataract surgery)
  - **Secondary objective:** To compare the rate of dry eye symptoms between Group 1 and Group 2 at 1 week and 1 month after cataract surgery. To compare the rate of dry eye disease (DED, Signs and symptoms) between Group 1 and Group 2 at 1 week, 1 and 3 months after cataract surgery.
- Vergleich der Rate der Symptome des trockenen Auges zwischen Gruppe 1 und Gruppe 2 1 Woche und 1 Monat nach der Kataraktoperation. Vergleich der Rate der Erkrankung des trockenen Auges (DED, Anzeichen und Symptome) zwischen Gruppe 1 und Gruppe 2 1 Woche, 1 und 3 Monate nach der Kataraktoperation.

## 3 Investigational plan

---

### 3.1 Design

Prospective, single-centre, controlled, randomized, observer-masked study

### **3.2 Selection of study population**

Participants will be selected by the clinical investigators at the out-patient clinics of the Department of Ophthalmology of the Hanusch Hospital and the connected health centres of the ÖGK, Vienna.

#### **3.2.1 Number of subjects**

For sample size calculation we used the data published earlier by Villani et al.[1] In the study 50% of the patients with an OSFI score higher than 0.3 (high risk group) developed dry during the study period. The rate was 9.6% in the group with an OSFI score lower than 0.3. These two proportions were used to calculate the sample size. We assume a clinical benefit of the lubrication drops if the rate of occurrence of dry eye in the high-risk group is reduced close to the value of the low-risk group (15%).

Using an alpha error of 0.05 and a power of 80 % we need to include 27 in group 1 and group 2. Due to the long study period, we expect a dropout rate of 30%. Therefore, we need to include 39 patients in group 1 and group 2. 39 patients will be included in group 3.

In total 117 patients will be enrolled into the study.

#### **3.2.2 Pre-study screening**

The following examination will be carried out in each subject:

- Ophthalmic examination
  - Visual acuity
  - Slit lamp biomicroscopy
    - Tear film break up time
    - Meibomian gland expressibility
    - Lipcof
  - OSFI Score
  - Meibography classification using the Meiboscore
  - Indirect ophthalmoscopy
  - Fundoscopy

#### **3.2.3 Inclusion criteria**

- Age older than 18 years
- Cataract surgery scheduled in one or both eyes
- Scheduled for monofocal or monofocal-toric IOL implantation
- OSDI lower than 14
- OSFI higher or equal to 0.3 – *Group 1 and Group 2*
- OSFI lower than 0.3 – *Group 3*

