### **3.2.4 Exclusion criteria**

- Presence of dry eye symptoms preoperatively
- Occurrence of complications during surgery
- Usage of systemic antibiotic therapy
- Any pathology of the ocular surface except dry eye disease (e.g. corneal scarring, cornea ectasia)
- Ocular surgery within prior 3 months
- Ocular injury within prior 3 months
- Ocular herpes of eye or eyelid within prior 3 months
- Active ocular infection
- Active ocular inflammation or history of chronic, recurrent ocular inflammation within prior 3 months
- Eyelid abnormalities that affect lid function
- Ocular surface abnormality that may compromise corneal integrity
- Pregnancy

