#### **3.3.1.1 Study schedule**

- Visit 1 - Screening
- Visit 2 - Baseline (prior to cataract surgery, within 30 days after screening)
- Visit 3 - Follow up 1 – (7±1 days after cataract surgery)
- Visit 4 - Follow up 2 – (30±7 days after cataract surgery)
- Visit 5 - Follow up 3 – (90±7 days after cataract surgery)

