### **3.3.1.5 Withdrawal and replacement of subjects**

Subjects must be withdrawn under the following circumstances:

- at their own request
- use of forbidden medication
- development of an Exclusion Criterion during study participation

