## **3.4 Variables and biometric methods**

### **3.4.1 Outcome variables**

**Primary Endpoint:** Rate of dry eye symptoms defined by OSDI  $\geq 13$  at 3 months

**Secondary Endpoints:** Rate of DED defined by OSDI  $\geq 13$  plus at least one of the following:

Presence of ocular surface staining, TFBUT  $< 10$ s at 1 week, 1 and 3 months

Comparison of dry eye related parameters between the groups: TFBUT, Staining scores (modified Oxford Grading Scale) at 1 week, 1 and 3 months

Change of dry eye related parameters during the study period (baseline, 1 week, 1 and 3 months) in the study eye: TFBUT, Staining scores (modified Oxford Grading Scale)

Change of OSDI score during the study period (baseline, 1 week, and 3 months)

**Exploratory Endpoints:** Comparison of dry eye symptoms rate DED rate between Group 1, Group 2 and Group 3, BCVA, IOP, Concomitant medication and Adverse Events

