### **4.2 Ocular surface disease index – OSDI**

The OSDI Questionnaire is a standardized questionnaire to evaluate the subjective disease burden caused by dry eye syndrome. The patients answer up to 12 questions regarding their symptoms. Thereafter, the OSDI Score is calculated.

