## 5 Schedule of Events

| Visit name                            | VISIT 1   | VISIT 2  | VISIT 3     | VISIT 4     | Visit 5     |
|---------------------------------------|-----------|----------|-------------|-------------|-------------|
| Visit date                            |           | Day 0    | Day 7       | Month 1     | Month 3     |
| Visit Description                     | Screening | Baseline | Follow up 1 | Follow up 2 | Follow up 3 |
| Visit date window                     | -30d to 0 | Day 0    | Day7 ± 1    | Day 30 ± 7  | Day 90 ± 7  |
| Informed consent                      | x         |          |             |             |             |
| Demographic data a         | x         |          |             |             |             |
| Medical history                       | x         |          |             |             |             |
| Prior medication b         | x         |          |             |             |             |
| Eligibility check                     | x         |          |             |             |             |
| Urine pregnancy test c     | x         |          |             |             |             |
| BCVA (ETDRS Chart)                    | x         | x        | x           | x           | x           |
| Intra ocular pressure                 | x         | x        | x           | x           | x           |
| Slit Lamp Examination                 | x         | x        | x           | x           | x           |
| Randomization                         | x         |          |             |             |             |
| OSDI score                            | x         | x        | x           | x           | x           |
| OSFI score                            | x         |          |             |             |             |
| DEQ 5                                 | x         |          |             |             |             |
| Meibography                           | x         |          |             |             |             |
| Photograph of the anterior segment    |           | x        | x           | x           | x           |
| Fluorescein/Lissamin green staining   | x         | x        | x           | x           | x           |
| Meibum expressibility                 | x         | x        | x           | x           | x           |
| Break up time                         | x         | x        | x           | x           | x           |

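### Entry admits OSDI below 14 while the primary event starts at 13, and no rule says what happens to a patient at 13 or more at Visit 2, before surgery

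*Protocol*

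**What the plan says.** Five parts of the Protocol bear on who may enter and who counts as an event.

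- Section 3.2.3 sets the symptom limit for entry, in all three groups, at "OSDI lower than 14".
- Section 3.2.4 excludes "Presence of dry eye symptoms preoperatively". It gives no score and no visit.
- Section 3.4.1 gives the primary endpoint as "Rate of dry eye symptoms defined by OSDI $\geq 13$ at 3 months". This is the only place where the protocol defines dry eye symptoms.
- Section 3.3.1.1 places Visit 2 "prior to cataract surgery, within 30 days after screening". The table in section 5 marks the eligibility check and randomisation at Visit 1 only, and OSDI at every visit from 1 to 5.
- Section 3.3.1.5 requires withdrawal on "development of an Exclusion Criterion during study participation".

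On the score itself, section 4.2 says only that "The patients answer up to 12 questions regarding their symptoms" and that a score is then calculated. It gives neither a formula nor a rounding rule.

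**The concern.** The trial is about onset. Section 1.1 presents the OSFI as a predictor of developing dry eye in people who do not have it, and section 3.2.1 takes its 50% from patients who developed dry eye during the cited study. An endpoint that is simply a score of 13 or more at 3 months measures onset only if everyone starts below 13.

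The criteria do not secure that, for two separate reasons. First, the entry limit and the event limit overlap between 13 and 14, and the exclusion that might close the gap has no cut-off. Second, entry is decided at screening. OSDI is measured again before surgery, but no entry rule names that score. Patients already at 13 or more before surgery are not at risk of onset. If kept, they add events to both arms, shrink the difference between them, and change what the reported rate means. If withdrawn, they are lost after randomisation.

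**Working it through.** **Step 1: the three cut-offs side by side.** For a preoperative score from 13 to below 14:

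| Rule | Section | Result |
|---|---|---|
| Inclusion, OSDI < 14 | 3.2.3 | admitted |
| Exclusion, preoperative symptoms, read as OSDI ≥ 13 | 3.2.4 with 3.4.1 | barred |
| Primary event, OSDI ≥ 13 | 3.4.1 | already met |

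The three rules cannot all be applied to this patient consistently.

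**Step 2: how wide the overlap is.** Assume the usual formula (not in the protocol): score = sum × 25 / k, where k is the number of items answered.

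- k = 12: the neighbouring values are 6 × 25 / 12 = 12.5 and 7 × 25 / 12 = 14.58, so nothing falls in the band.
- k = 11: 6 × 25 / 11 = 13.64.
- k = 9: 5 × 25 / 9 = 13.89.
- Every other k from 1 to 12 skips the band (for k = 10, the values go from 12.5 to 15).

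So the overlap holds two possible values, both needing unanswered items, which section 4.2 allows. This is for unrounded scores. If scores were stored as whole numbers with halves rounded up, 12.5 would become 13 and fall in the overlap.

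**Step 3: the Visit 2 gap.** A patient is eligible and randomised at Visit 1, and scores 13 or more at Visit 2, up to 30 days later and before surgery. Two readings are open.

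- The exclusion means OSDI ≥ 13. An exclusion criterion has then developed during participation, and section 3.3.1.5 requires withdrawal, after randomisation. Section 3.4.2.2 leaves missing observations out of the analysis.
- The exclusion is a clinical judgement, or is taken as met by the limit of 14. The patient stays, and is a primary event if still at 13 or more at 3 months.

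The protocol does not say which applies.

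**Step 4: the plan's own sample size.** Inputs from section 3.2.1: p1 = 0.50, p2 = 0.15, alpha 0.05 (sidedness not stated; two-sided reproduces the figure), power 80%, dropout 30%. With pooled variance and no continuity correction:

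n = [1.960 × √(2 × 0.325 × 0.675) + 0.842 × √(0.50 × 0.50 + 0.15 × 0.85)]² / 0.35² = 26.9, rounded up to 27.

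Power at 27 is 80.2%. Then 27 / 0.70 = 38.6, rounded up to 39, and 3 × 39 = 117. All stated figures reproduce.

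**Step 5: illustration if such patients are kept.** Let f be the share of patients at 13 or more before surgery. The documents do not give f. Assume that all of them are events at 3 months in both arms, so each rate becomes p′ = f + (1 − f) × p. For f = 5%: 0.05 + 0.95 × 0.50 = 0.525 and 0.05 + 0.95 × 0.15 = 0.1925.

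| Assumed f | Group 1 | Group 2 | Power at 27 per arm | n per arm for 80% | Enrolled per arm |
|---|---|---|---|---|---|
| 0% | 50% | 15% | 80.2% | 27 | 39 |
| 2% | 51% | 16.7% | 77.5% | 29 | 42 |
| 5% | 52.5% | 19.25% | 73.4% | 32 | 46 |
| 10% | 55% | 23.5% | 66.8% | 37 | 53 |

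**Step 6: illustration if they are withdrawn.** The allowance is 39 − 27 = 12 per arm. If Visit 2 withdrawals come on top of the 30% dropout, the evaluable number per arm is 39 × (1 − f) × 0.70: 26.8, 25.9 and 24.6 for f = 2%, 5% and 10%, against the 27 required. If the 30% was meant to cover them, there is no shortfall.

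**The case against.** The best defence is that the exclusion already does the work. An exclusion overrides an inclusion; read with the only definition in the protocol, it bars anyone at 13 or more, and the withdrawal rule in section 3.3.1.5 catches those who reach 13 by Visit 2. On that reading no such patient is counted as a postoperative event. This is a fair reading, and it rules out any claim that such patients certainly enter. It does not remove the problem. The exclusion names no score, and section 3.2.4 also exempts dry eye disease from its bar on ocular surface pathology, although section 3.4.1 defines that disease as OSDI ≥ 13 plus a sign. A site could reasonably work to the one explicit number, 14. Where the defence does hold, it turns the Visit 2 cases into losses after randomisation.

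A second objection is that the effect is small and not a bias towards treatment. For the threshold mismatch alone, the size may indeed be close to nil (step 2). The power figures belong to the Visit 2 gap, not to the mismatch, and they assume that every such patient stays an event whichever arm they are in, which is pessimistic. Group 2's lubricant starts after surgery, so randomisation should spread these patients over both arms. The expected harm is dilution of the comparison.

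A reader might also infer that the Visit 2 OSDI goes unused. It does not: sections 3.4.1 and 3.4.2.2 use baseline OSDI in the analysis of change over visits. What is missing is its use at entry.

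**Conclusion.** The point holds as a contradiction between criteria together with an unsettled case. Sections 3.2.3, 3.2.4 and 3.4.1 give conflicting answers for a score from 13 to below 14. Sections 3.2.4, 3.3.1.5 and 5 leave open what happens to a patient at 13 or more at Visit 2. Such patients can enter already meeting the endpoint; the documents give no OSDI distribution, so they do not show that any will, or how many.

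The overlap itself is narrow, on the assumed formula and unrounded scores. The Visit 2 gap is the larger route. Its cost depends wholly on an unknown share: from about 2 to 3 points of power at an assumed 2% to about 13 points at 10%, in the worst case where all of these patients remain events.

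A reader might infer that the sample size is wrong. It is not: 27, 39 and 117 follow from the stated inputs, and aligning the cut-offs leaves them unchanged, because 50% and 15% are used as rates of new onset. Nor does this point require randomisation to wait until after surgery. Having the Visit 2 score in hand first is enough.

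**What to change.** Use one cut-off throughout. Set inclusion at OSDI below 13, and define the preoperative-symptom exclusion in section 3.2.4 as OSDI ≥ 13, so that both match the primary endpoint. Make the Visit 2 preoperative OSDI an entry condition for all three groups, checked before randomisation, so that a failure is a screen failure. State the OSDI formula and whether scores are rounded. Reconcile sections 3.2.3, 3.2.4, 3.3.1.5, 3.4.1 and the section 5 table accordingly, including its footnotes that divide prior from concomitant medication at randomisation.

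If randomisation has to stay at Visit 1, the protocol should at least state how patients with a Visit 2 OSDI of 13 or more are handled in the primary analysis.

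The cut-off changes are a matter of wording, and the Visit 2 questionnaire is already scheduled. The real costs are moving randomisation from Visit 1 to after the Visit 2 OSDI, which falls on the day of surgery, and some extra screen failures. To keep 39 per group when a share f fails at Visit 2, 39 / (1 − f) patients must pass Visit 1: 40, 42 or 44 per group at the assumed 2%, 5% or 10%.

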### **3.2.4 Exclusion criteria**

- Presence of dry eye symptoms preoperatively
- Occurrence of complications during surgery
- Usage of systemic antibiotic therapy
- Any pathology of the ocular surface except dry eye disease (e.g. corneal scarring, cornea ectasia)
- Ocular surgery within prior 3 months
- Ocular injury within prior 3 months
- Ocular herpes of eye or eyelid within prior 3 months
- Active ocular infection
- Active ocular inflammation or history of chronic, recurrent ocular inflammation within prior 3 months
- Eyelid abnormalities that affect lid function
- Ocular surface abnormality that may compromise corneal integrity
- Pregnancy

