**3.3.1.4 Randomization**

The eye scheduled for cataract surgery will be selected as the study eye. Patients included into the study are allocated to one out of three groups. Patients with an OSFI score equal or higher than 0.3 (high risk) will be randomized into group 1 or 2, using an online randomisation tool (<https://randomizer.org>, list randomizer) by an unmasked member of the study staff.

**Group 1** receives the routine postoperative treatment (*Yellox eye drops* bid for four weeks after surgery, Bausch and Lomb, Germany), serves as the **standard of care group**.

**Group 2** is the treatment group and will receive *Systane Hydration MDPF eye drops* (Alcon, USA) in both eyes four times a day starting after surgery until the three-month visit in addition to the routine treatment (*Yellox eye drops* bid for four weeks after surgery, Bausch and Lomb, Germany). Allocation to group 1 and group 2 will be randomized. All patients will receive a log to document the use of eye drops. Group 2 serves as the **treatment group**.

Patients with OSFI score below 0.3 (low risk) will be included in **group 3** and serve as a **reference group**. All patients are asked not to use any other eye drops other than their routine therapy (*Yellox eye drops* bid for four weeks after surgery, Bausch and Lomb, Germany). In case of significant complaints due to dry eye a rescue medication will be offered to the patient.

**Group 1 (Standard of care):** OSFI higher or equal 0.3, *Yellox eye drops* twice a day for 4 weeks

**Group 2 (Treatment):** OSFI higher or equal 0.3, *Yellox eye drops* twice a day

for 4 weeks and *Systane Hydration MDPF* eye drops 4 times a day for the whole study period (3 month)

**Group 3 (Reference):** OSFI lower 0.3, *Yellox eye drops* twice a day for 4 weeks

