| Concomitant medication d   |           | x        | x           | x           | x           |
| Adverse event collection e |           | x        | x           | x           | x           |
| Cataract surgery                      |           | x        |             |             |             |

a.....Age, gender, race

b.....until randomization

c.....in women of childbearing potential only

d.....as of randomization

e.....as of informed consent signature

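### Patients are randomised at screening, but two exclusion criteria can first be met after that, before any study drop is given, so randomised patients are removed from the Group 1 versus Group 2 comparison

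*Protocol*

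**What the plan says.** All references are to the protocol.

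- **Time of randomisation.** In section 5 the row "Randomization" carries one mark, under Visit 1 (screening). Section 3.3.1.4 describes how Groups 1 and 2 are allocated but gives no other time.
- **Time of baseline and surgery.** Section 3.3.1.1 lists "Visit 2 - Baseline (prior to cataract surgery, within 30 days after screening"). Section 5 places surgery at the same visit, Day 0.
- **Start of the study drops.** Section 3.3.1.4 has Group 2 use them "four times a day starting after surgery until the three-month visit".
- **Exclusions.** Section 3.2.4 includes "Occurrence of complications during surgery" and also the presence of dry eye symptoms before surgery.
- **Consequences.** Section 3.3.1.5 requires withdrawal of a patient who comes to meet an exclusion criterion while in the study. Its title mentions replacement, but its text gives no replacement rule. Section 3.4.2.2 omits missing observations from the analysis.
- **Sample size.** Section 3.2.1 assumes rates of 50% and 15%, alpha 0.05 and 80% power, giving 27 per group. A 30% dropout, explained by the length of the study, raises this to 39 per group, or 78 high-risk patients.

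**The concern.** Randomisation protects a comparison best when eligibility is settled first and treatment starts soon afterwards. Here allocation can come up to 30 days before the last eligibility fact is known. Whatever happens in that interval, such as a complication in theatre or symptoms reported at Visit 2, becomes a loss after randomisation. Because withdrawal is mandatory, the outcome is not collected. A later analysis plan can define analysis sets, but it cannot recover those outcomes.

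Two things are at stake. One is size: patients count towards the 39 per group and contribute nothing to the three-month comparison. The other is the integrity of the comparison. The trial is observer-masked only and Group 1 gets no study drops, so a patient who has been told the allocation is not masked. The Visit 2 OSDI is patient-reported and is collected after allocation exists. A decision to exclude on it could also be taken when staff already know the arm.

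**Working it through.** **1. Is the Visit 1 mark a slip in the table?** The footnotes in section 5 suggest not. Footnote b closes prior medication at randomisation, and that row is marked only at Visit 1. Footnote d opens concomitant medication at randomisation, and that row starts at Visit 2. Both fit randomisation at screening.

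**2. Which exclusions can arise after allocation?** The order of events is:

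| Step | Visit | Source |
|---|---|---|
| Eligibility check, OSFI, first OSDI, randomisation | 1 (up to 30 days before Day 0) | 5 |
| Baseline OSDI and signs | 2 | 3.3.1.1, 3.3.1.2, 5 |
| Cataract surgery | 2 (Day 0) | 5 |
| First Group 2 drop | after surgery | 3.3.1.4 |

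A surgical complication falls between the third and fourth steps. New preoperative symptoms can appear at the second. Both come after randomisation and before treatment, and section 3.3.1.5 then requires withdrawal. That the Visit 2 OSDI can trigger the symptom exclusion is a reading: section 3.2.4 does not say how, or at which visit, those symptoms are judged.

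**3. Reproduce the planned size.** For two proportions, two-sided, pooled variance under the null and no continuity correction, with p1 = 0.50, p2 = 0.15, mean 0.325 and difference 0.35:

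n = [1.960 × √(2 × 0.325 × 0.675) + 0.842 × √(0.50 × 0.50 + 0.15 × 0.85)]² / 0.35²

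= [1.298 + 0.517]² / 0.1225 ≈ 26.9, so 27 per group.

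Power at 27 is 80.2%. Dropout: 27 / 0.70 = 38.6, so 39. Both stated figures reproduce.

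**4. Size of the surgical loss.** The protocol gives no complication rate. A range of 2% to 5% is assumed.

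- Patients excluded after allocation: 78 × 0.02 = 1.6 and 78 × 0.05 = 3.9, so about 2 to 4.
- If these come on top of the 30%, the evaluable number per group is 39 × 0.98 × 0.70 = 26.8 or 39 × 0.95 × 0.70 = 25.9.
- Rounded down to 26 and 25, power is 78.6% and 76.9%. Rounding 25.9 down to 25 makes the second figure slightly pessimistic.
- Keeping 27 evaluable would need 27 / (0.98 × 0.70) = 39.4, so 40 per group, or 27 / (0.95 × 0.70) = 40.6, so 41.
- If the 30% already includes these losses, 39 × 0.70 = 27.3 still holds and power is unchanged. Section 3.2.1 does not say which case applies.

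The document gives no basis for a figure on exclusions for new symptoms at Visit 2, so none is added.

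**The case against.** The strongest case on the other side is that little is lost and nothing is shown to be biased.

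- **Losses before treatment.** Drops not yet given cannot cause a complication or a cancelled operation. A reader might infer that the randomised comparison is broken. The protocol does not support that for the surgical losses, which are unlikely to depend on arm and mainly cost patients. This objection stands. It does not cover exclusions that involve judgement once the arm is known.
- **Baseline after allocation.** A reader might infer that no clean baseline exists. That goes too far. Section 5 also schedules OSDI, staining, meibum expressibility and break-up time at Visit 1. The OSFI score that determines entry to the randomised groups itself uses break-up time and expressibility. Section 3.3.1.2 has a masked investigator perform the baseline dry eye examination, and the primary endpoint uses only the three-month OSDI. Nothing says that patients learn their arm at Visit 1. What remains is the Visit 2 OSDI, which is patient-reported and enters the secondary change analyses.
- **The dropout allowance.** A reader might infer that surgical losses use up the 30%. At an assumed 5% they are one sixth of it (5 / 30).
- **Who randomises.** Allocation is done "by an unmasked member of the study staff". A reader might take this as a fault in itself. In an observer-masked trial it is normal, because it keeps the assessor masked. How the list is made and concealed is a separate question and adds no weight here.

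**Conclusion.** The point holds in limited form. Followed as written, the protocol removes randomised patients from the Group 1 versus Group 2 comparison before any study drop is given. The order of events is fixed by the protocol's own schedule, footnotes, exclusion list and withdrawal rule, and needs no outside assumption. For the symptom exclusion it also rests on reading the Visit 2 OSDI as able to trigger it.

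The size does rest on an assumption. At a complication rate of 2% to 5%, about 2 to 4 of 78 patients are lost and power falls from 80% to about 77% to 79% if the losses are additional to the 30% dropout. If the 30% covers them, the sample size is unaffected. The possible bias is confined to exclusions decided, and the Visit 2 OSDI collected, after allocation exists. The protocol permits this but does not show that it would happen. The change is worth making because it is cheap and cannot be made for patients already randomised. Severity: should be fixed.

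**What to change.** In section 5, move the randomisation mark from Visit 1 to Visit 2. In section 3.3.1.4, state that allocation takes place after the baseline examinations and after surgery has ended without an excluding complication, but before the first study drop, with eligibility confirmed at that moment. Align footnotes b and d with the new time. No dose, exclusion or withdrawal rule needs to change.

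Costs:

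- The drops must be ready for dispensing on the day of surgery.
- Prior medication, now recorded only at Visit 1, must be updated at Visit 2, or up to 30 days go unrecorded.
- A few more patients must be screened to randomise 39 per group. For complications alone, 78 / 0.98 = 79.6 and 78 / 0.95 = 82.1, so 80 to 83 high-risk patients instead of 78, plus any lost to cancelled surgery or new symptoms.

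No extra visit is needed. Any gain in power over the plan should not be claimed as free. If, say, 5 points of the 30% dropout fall before the end of surgery, 39 × 0.75 = 29.3 patients per group would be evaluable, with power of about 83%, but only because the patients lost before allocation are replaced at screening.
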